### Assessments

Demographic variables (age, sex, social conditions, education, connection to the labor market), previous treatment, medication, use of alcohol and/or narcotics, BMI, pregnancy, ability to attend treatment, and language skills are assessed at the first assessment interview with a therapist and by a psychiatrist or attending physician at their assessment interview (part of the clinical routine).

Eating disorder diagnosis is assessed at the trial assessment interview. Diagnosis is set using the EDE [38].

### The mini-international neuropsychiatric interview (MINI)

Present psychosis and depression, suicidal risk and abuse of alcohol, medicine and/or narcotics is assessed by a psychiatrist or attending physician at the patient’s initial assessment interview using the Mini International Neuropsychiatric Interview (MINI) [39]. MINI is a short structured diagnostic interview compatible with international diagnostic criteria, including the International Classification of Diseases (ICD-10) and the Diagnostic and Statistical Manual of Mental Disorders (DSM-IV) [39]. We are using a modified version of the authorized Danish version of the MINI 5.0. We have included the suicidality module from version 6.0.0 and have modified the alcohol dependence and/or alcohol abuse module to Danish norms. Previous studies of the psychometric properties of MINI have shown a good sensitivity, specificity, reliability, and validity [39].

### Standardized assessment of personality (SAPAS)

The possible presence of a DSM-IV recognized personality disorder is assessed with SAPAS [40] at the trial assessment interview. We are using a researcher-rated version of the questionnaire, which consists of eight dichotomously rated questions about the patient’s personality. A previous study indicated that a score of 3 or 4 on the SAPAS correctly identified the presence of a personality disorder in over 80% of 60 psychiatric in- and outpatients [40]. The same study reported that the internal consistency, test-retest reliability, sensitivity, and specificity were acceptable.

### Eating disorder examination (EDE) interview

Eating disorder symptoms are measured with the EDE interview [38,41]. The eating disorder examination is a widely used interview in eating disorders research and is considered ‘the gold standard’ in diagnosing eating disorders. We use the authorized Danish version of the eating disorder examination (EDE) interview (version 12), including the binge eating disorder module from version 16, as the secondary outcome measure and as a diagnostic tool [38,42].We use the global score to compare the groups post treatment.

A high degree of inter-rater reliability, internal consistency and discriminant validity has been reported [43]. The interviews are performed by five interviewers trained by an experienced clinician and researcher. The training consisted of two days at six hours per day.

### The outcome rating scale (ORS)

On the ORS [17], patients assess their wellbeing during the last week. The use of the ORS is described in the section about the feedback intervention.

### The symptom check list (SCL-90R)

Psychological problems and symptoms of psychopathology are measured with the authorized Danish version of the SCL-90R [44,45]. The SCL-90R is a multidimensional patient-reported questionnaire for measuring psychological distress or the degree of affective distress [44-46]. The Global Severity Index (GSI), which is the global score covering all 90 items, will be used in the trial. Internal validity has been tested and found acceptable for all subscales, besides psychoticism [46].

### Sheehan disability scale (SDS)

Functional impairment is measured with the SDS [47]. The SDS is a patient-rated measure of functional disability in work, social life, and family life. The SDS is a composite of three self-rated items of family, work and social impairment in the previous two weeks [48]. Studies of the psychometric properties of the SDS have demonstrated an acceptable reliability, sensitivity to change and construct validity [48].

### WHO-five wellbeing index (WHO-5)

Psychological wellbeing is measured with WHO-5 [49]. The WHO-5 consists of five items that cover positive mood (feeling in good spirits, feeling relaxed), vitality (being active and waking up fresh and rested), and being interested in things. The time frame is the past two weeks and a high score indicates good wellbeing, with a low score indicating the opposite [49]. Studies have found the scale to have a good reliability and excellent validity [50].

### Suicide and self-harm

To assess the occurrence of self-harm behaviour, we have selected seven questions from the Self-Harm Inventory (SHI) [51]. The SHI is in its full length a one-page, 22-item, yes/no questionnaire that explores respondents’ history of self-harm. Each item is preceded by the phrase, ‘Have you ever intentionally, or on purpose…’ followed by (in our modified version): 1: ‘Cut yourself’; 2: ‘Burned yourself’; 3: ‘Hit yourself’; 4: ‘Banged your head’; 5: ‘Scratched yourself’; 6: ‘Prevented wounds from healing’; 7: ‘Attempted suicide’. The time frame is during the treatment period and the questions are presented orally by the assessor at the end of intervention. A recent study comparing six commonly used scales on deliberate self-harm demonstrated that the SHI was psychometrically sound [52].

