### Objective

The trial’s objective is to examine the benefits and harms of continuous feedback on treatment progress and alliance in group therapy to patients and therapists. We hypothesize that continuous feedback with subsequent adjustments of the treatment, will increase treatment attendance and treatment outcome.

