### Participant withdrawal

Participation in the trial is voluntary and patients can withdraw from the trial at any time, without any implications for current or future treatment at Stolpegaard Psychotherapy Centre. The participants are kindly asked to specify which aspects of the trial they wish to withdraw from: the intervention, participation in follow-up assessments, or complete withdrawal from the trial. The options are described in the written patient information.

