### Outcomes

The primary outcome is treatment attendance in the intervention period, defined as a rate (number of attended therapy sessions divided by the number of planned therapy sessions). If a patient ends therapy prematurely, and this is in accordance with the therapists, the number of attended sessions will be set equal to the planned number of sessions. The secondary outcome is the global score of eating disorder examination (EDE) interview, assessed at the end of intervention. The mean score in the two intervention groups are compared.

The exploratory outcomes are: ORS, the Symptom Check List (SCL-90R), the Sheehan Disability Scale (SDS), the WHO-Five Wellbeing Index (WHO-5), and suicide and self-harm.

For all outcomes except the ORS, the scores obtained in the two intervention groups after the end of the treatment are compared. With regard to the ORS, the last available score for each patient in the two groups is compared (see further description of these outcomes below).

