### Follow-up assessments

A follow-up assessment will be performed within three years after the end of the intervention. The scores of all secondary and explorative outcome measures in the two groups at the longest follow-up (up to 36 months) are compared. See Table 2 for the method and timing of the assessment.

**Table 2 T2:** Method and timing of assessment

	**1. Initial assessment (clinical routine)**	**2. Psychiatric and somatic assessment (clinical routine)**	**3. Trial assessment**	**4. Start of treatment**	**5. During treatment**	**6. End of treatment**	**7. Follow-up**
Sociodemographic data	X						
Eating Disorder Examination (EDE)			X			X	X
Mini International Neuropsychiatric Interview (MINI)		X					
Standardized Assessment of Personality – Abbreviated Scale (SAPAS)			X				
Sheehan Disability Scale (SDS)			X			X	X
Symptom Check List (SCL-90-R)	X					X	X
The Outcome Rating Scale (ORS)				X	X		X
WHO-Five Well Being Index (WHO-5)	X					X	X
Questions about self-harm and suicide						X	X

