### Randomization and blinding

The Copenhagen Trial Unit (CTU) will be responsible for the central randomization. They have no clinical involvement in the trial. Randomization is carried out according to a computer-generated allocation sequence with a varying block size kept unknown to the investigators. After each patient is assessed to be eligible for the trial, the trial secretary will call CTU, provide a personal pin code and receive the randomization result.

The randomization is stratified for eating disorder diagnosis (BN, EDNOS or BED) and treatment type (basic or elaborate). Patients and therapists are naturally aware of the patient allocation but secondary outcome assessment (EDE), statistical analyses, and drawing of conclusions will be done with the blind intact. Blinding is maintained by instructing the intervention team to withhold patient information from the research team. The research team has no clinical contact with the patients from assessment to end of intervention, and the assessors have no knowledge about the patient’s randomization status at the end of intervention. In order to prevent the risk of bias, such as when therapists are assessing patient withdrawal, we have a blinded assessor counting the attendance rate and checking each patient’s medical file. In order to prevent actual bias, the research team is not present in supervision or when the therapists are discussing patients at conferences.

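### The suicide and self-harm outcome is collected only by interviewing the patient over an undefined treatment period, so completed suicide cannot be counted and the exposure window may differ by arm

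*Protocol article*

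**What the plan says.** The Objective section covers both directions of effect: "The trial’s objective is to examine the benefits and harms of continuous feedback on treatment progress and alliance in group therapy to patients and therapists". In the Outcomes section under Methods/design, the exploratory list ends with "the WHO-Five Wellbeing Index (WHO-5), and suicide and self-harm". This is the only entry there directed specifically at harm.

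The Suicide and self-harm section describes the measurement as seven yes/no items taken from the Self-Harm Inventory. Only the seventh concerns suicide, and it asks about attempts. On window and mode it says: "The time frame is during the treatment period and the questions are presented orally by the assessor at the end of intervention".

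Table 2 marks these questions at end of treatment and again at follow-up. The Follow-up assessments section adds: "The scores of all secondary and explorative outcome measures in the two groups at the longest follow-up (up to 36 months) are compared". It gives no recall window for the repeat.

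Two other sections bear on the point. Under Participant withdrawal, patients are asked to "specify which aspects of the trial they wish to withdraw from: the intervention, participation in follow-up assessments, or complete withdrawal from the trial". Under Randomization and blinding, to guard the attendance count against bias, "we have a blinded assessor counting the attendance rate and checking each patient’s medical file". No use of the file for suicide or self-harm is described.

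**The concern.** Three features of the measurement need attention.

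1. **Completed suicide.** The outcome is named for suicide as well as self-harm, but a living respondent has to supply every answer. The gravest event in the outcome's own name has no route into the data.
2. **Patients who leave treatment.** Capture depends on the patient attending an interview. The trial was designed because patients with eating disorders often leave treatment, so the loss could be sizeable. It could also differ by arm if feedback changes who stays.
3. **The window.** The recall period is tied to treatment, and the trial expects feedback to change treatment attendance. If the period is the patient's actual stay, the arm that stays longer has more time in which a yes can occur.

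At stake is whether a reported absence of difference, or an excess under feedback, can be read as a statement about harm.

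**Working it through.** **The plan's own figures.** The article gives no event rate, power or sample size for suicide and self-harm. The sample size for attendance does reproduce: a difference of 3 sessions and SD 6 give a standardised difference of 0.5. A two-sided 5% t-test then needs 63.8 per group for 80% power and 85.03 for 90%, against the stated 64 and 85.

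**Completed suicide.** The source is an oral interview, and the only suicide item concerns attempts. The follow-up repeat is the same questions put to the same person. No second source is described, so a death by suicide contributes nothing at either time point.

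**Patients at risk of no harm data (worst case).** The Background cites 23.9% dropout in eating disorders. If that rate applied here and every such patient missed the interview:
- 0.239 × 128 = 30.6, about 31 patients (0.239 × 64 = 15.3 per arm)
- 0.239 × 170 = 40.6, about 41 patients (0.239 × 85 = 20.3 per arm)

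**Window artefact, if the period is the actual stay.** Inputs from Sample size estimation: historical mean 13.58 sessions and an expected gain of at least 3, so 13.58 + 3 = 16.58. Assume a constant hazard, no true effect of feedback, and time in treatment proportional to sessions attended.
- Ratio of exposure: r = 16.58 / 13.58 = 1.221
- Feedback-arm proportion: 1 − (1 − p)^r, where p is the control proportion

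The article gives no value for p, so a range is assumed:

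| Control p | Feedback arm | Difference (points) | Ratio |
|---|---|---|---|
| 5% | 6.1% | 1.1 | 1.21 |
| 10% | 12.1% | 2.1 | 1.21 |
| 20% | 23.8% | 3.8 | 1.19 |
| 30% | 35.3% | 5.3 | 1.18 |
| 40% | 46.4% | 6.4 | 1.16 |

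The chance that this artefact alone gives a significant excess under feedback (normal approximation, two-sided 5%) runs from 4.5% to 10.9% at 64 per arm and from 4.9% to 13.1% at 85 per arm. For example, at p = 20% and 64 per arm the standard error is √[(0.20 × 0.80 + 0.2385 × 0.7615)/64] = 0.073. Then z = 0.0385/0.073 = 0.53, and Φ(0.53 − 1.96) is about 0.076.

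**Window artefact, if the period is the planned course.** Both arms within a stratum have the same window, so r = 1 and the artefact is zero. The text does not say which reading applies.

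**The case against.** The other side has several good points, and most of them limit the concern rather than remove it.

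- **The end-of-treatment interview is not the only occasion.** A reader might infer that it is, but Table 2 repeats the questions at follow-up, so a patient missed once may be reached later. This stands, though it cannot help with a death.
- **Dropouts are not necessarily missed.** A patient may leave the intervention and stay in the assessments, the analyses are by intention to treat, and nothing confines the interview to completers. The counts of 31 and 41 are therefore upper cases built on a background rate. The absence of a missing-data rule for this exploratory outcome is not a fault in itself, since an analysis plan would usually supply it.
- **The text does not say each patient's own stay.** The Standard treatment section gives treatment length by programme, about 10 months or 12 to 14 months, and randomisation is stratified by treatment type. A planned-course reading is reasonable.
- **Attendance is not time in treatment.** The hypothesis concerns sessions attended out of sessions planned. Three more sessions could come from fewer absences over the same months, which would leave the window unchanged. The ratio of 1.2 is a conditional illustration, not an estimate.
- **Other outcomes can show deterioration**, because they are tested two-sided. It would go too far to say that the harms objective is wholly unanswered.
- **Death reporting may sit in the full protocol**, since the article cites ethics approval and good clinical practice. That is possible, but reporting a death for safety does not make it part of the compared outcome, whose described source is the interview.

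**Conclusion.** The point holds in a limited form. On the method described, completed suicide cannot be counted in an outcome that bears its name, and this rests on no assumption beyond the stated source. Patients who leave treatment are at risk of having no harm data, which is weaker than saying that they are excluded. The window is poorly fixed. Its effect ranges from none, under a planned-course reading, to an apparent ratio of about 1.16 to 1.21 under an actual-stay reading with a constant hazard and sessions standing in for time. A reader might infer that feedback is bound to look more harmful, but the document does not support that, because it depends on one reading of undefined text and the effect is modest. The outcome is exploratory, so the primary and secondary results are untouched. The change is still worth making, because the harms comparison is weaker than it needs to be and better wording is cheap.

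**What to change.** In the Suicide and self-harm section:

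1. Replace the treatment-period wording with one calendar window starting at randomisation, the same in both arms within each treatment-type and diagnosis stratum. It could run, for example, to the scheduled end of the planned programme, whether or not the patient is still attending. State the window for the follow-up repeat as well.
2. Ask the interview items over that window of all randomised patients, including those who stopped treatment.
3. Add deaths by suicide and suicide attempts recorded in the medical file, which the blinded assessor already checks for attendance, and count them in the outcome for all randomised patients.
4. Keep the interview as the main source for non-suicidal self-harm. File entries depend on how often staff see the patient, so making the file the main source would bring back an attendance-linked bias.

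The cost is a wording change and one extra extraction item in a file review already planned. File data may be incomplete once a patient has left the centre, and this should be acknowledged when the result is reported.

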### Follow-up assessments

A follow-up assessment will be performed within three years after the end of the intervention. The scores of all secondary and explorative outcome measures in the two groups at the longest follow-up (up to 36 months) are compared. See Table 2 for the method and timing of the assessment.

**Table 2 T2:** Method and timing of assessment

	**1. Initial assessment (clinical routine)**	**2. Psychiatric and somatic assessment (clinical routine)**	**3. Trial assessment**	**4. Start of treatment**	**5. During treatment**	**6. End of treatment**	**7. Follow-up**
Sociodemographic data	X						
Eating Disorder Examination (EDE)			X			X	X
Mini International Neuropsychiatric Interview (MINI)		X					
Standardized Assessment of Personality – Abbreviated Scale (SAPAS)			X				
Sheehan Disability Scale (SDS)			X			X	X
Symptom Check List (SCL-90-R)	X					X	X
The Outcome Rating Scale (ORS)				X	X		X
WHO-Five Well Being Index (WHO-5)	X					X	X
Questions about self-harm and suicide						X	X

### Procedures

#### **
*Trial conduct*
**

This trial will be conducted in compliance with the protocol approved by the regulatory authorities: The Regional Ethics Committee of the Capital Region (journal number H-3-2011-151) and the Danish Data Protection Agency (journal number 2007-58-0015), and according to good clinical practice and the Declaration of Helsinki in its latest form. No substantial deviation from the protocol will be implemented without the prior review and approval of the regulatory authorities except where it may be necessary to eliminate an immediate hazard to trial participants.

### Randomization and blinding

The Copenhagen Trial Unit (CTU) will be responsible for the central randomization. They have no clinical involvement in the trial. Randomization is carried out according to a computer-generated allocation sequence with a varying block size kept unknown to the investigators. After each patient is assessed to be eligible for the trial, the trial secretary will call CTU, provide a personal pin code and receive the randomization result.

The randomization is stratified for eating disorder diagnosis (BN, EDNOS or BED) and treatment type (basic or elaborate). Patients and therapists are naturally aware of the patient allocation but secondary outcome assessment (EDE), statistical analyses, and drawing of conclusions will be done with the blind intact. Blinding is maintained by instructing the intervention team to withhold patient information from the research team. The research team has no clinical contact with the patients from assessment to end of intervention, and the assessors have no knowledge about the patient’s randomization status at the end of intervention. In order to prevent the risk of bias, such as when therapists are assessing patient withdrawal, we have a blinded assessor counting the attendance rate and checking each patient’s medical file. In order to prevent actual bias, the research team is not present in supervision or when the therapists are discussing patients at conferences.

### Ethical considerations

This trial is carried out in order to improve treatment for patients with eating disorders. If the results support our hypothesis, the addition of feedback can have the potential of improving treatment outcome in diagnoses other than eating disorders. The control group receives a standardized treatment based on recommendations from the Danish National Board of Health [2] and on guidelines for treating eating disorders in the Capital Region of Denmark [29].

### Risks and benefits

There are no known or obvious risks concerning participation in this trial. The only inconvenience is that participants are required to spend more time on assessment than in clinical routine assessment (filling out questionnaires as well as attending an extra assessment interview pre and post treatment). The assessment provides additional information about the patient’s condition for the intervention team to use in the treatment process. Rating the feedback scales before and after each session can put an extra strain on patients and they are offered assistance in this process. The benefits are estimated to outweigh the risks.

### Statistical plan and data analysis

#### **
*Sample size estimation*
**

We are planning a trial of independent experimental participants and control participants randomized at a 1:1 ratio. Unpublished data (Stolpegaard Psychotherapy Centre, routinely collected data) from 138 patients with eating disorders at Stolpegaard Psychotherapy Centre indicate that the mean number of attended treatment sessions is 13.58 and the SD is 5.82 sessions. We expect to find that the participants in the experimental group attend at least three more sessions than the participants in the control group. Using a SD of six sessions, we need to include 64 participants in each group (total 128) to be able to reject the null hypothesis that number of attended treatment sessions in the experimental and control group is equal with probability (power) 80%. The type I error probability associated with the test of this null hypothesis is 5%. We also estimated the sample size using a power of 90%. This resulted in a total of 170 participants (2 × 85 participants). We therefore plan to recruit a minimum of 128 participants, and in order to reduce the risk of type II error, we will aim to recruit up to 170 participants, if possible in the 14 months recruitment period. Power and sample size calculations have been made using the PS Power and Sample Size Calculations program version 3.0.14 [53,54] (Dupont & Plummer, Nashville, USA).

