### Dropout and non-attendance in psychotherapy

The term ‘dropout’ refers to patients that choose to end treatment prematurely. It is a common phenomenon in psychotherapy. A recent comprehensive meta-analysis, analyzing 669 studies and 83,834 adult patients with a non-psychotic disorder, reported that, on average, 19.7% of patients dropped out of psychotherapy. The dropout proportion for a subsample of patients with eating disorders was even higher at 23.9% [5].

Previous research has indicated that patients who discontinue treatment prematurely exhibit poorer treatment outcomes [5,6]. In group therapy especially, dropout not only affects the patients themselves and their therapists, but can also have an adverse effect on the remaining group members, sometimes resulting in a ‘wave effect’ with dropouts begetting other dropouts [6].

Related to dropout is the phenomenon of irregular attendance to treatment sessions. It has been demonstrated that psychotherapy attendance is associated with the outcome of treatment [7-9] and, accordingly, the development and testing of interventions to increase attendance and prevent dropout from psychotherapy is highly relevant.

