### Structure

There are seven patients and two therapists in each group. The groups are slow-open, that is, open to new patients as others end treatment. Central to the treatment is a food diary that patients are asked to keep and discuss in the group therapy sessions. Patients are weighed before each session and weight fluctuation is monitored and addressed in the case of rapid weight gain or weight loss. The patients are encouraged to set individual goals for the treatment, typically concerning food, body and appearance, relations, and future [36]. The duration of a group session is 150 minutes.

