### Outcomes

The primary outcome is the rate of attendance. It is defined as the number of group sessions the patient has attended over the number of planned sessions (20 or 25 sessions). If at group session # n (n <20) the therapist decides that the patient needs not attend further sessions, the number of planned sessions is set equal to n. When a patient discontinues treatment early, the therapists decide whether this is in accordance with the treatment plan (categorized as ‘planned withdrawal’ or ‘unplanned withdrawal’).

In the analysis of the rate data, the model fit of a Poisson model and a negative binomial model both with offset equal to log (number of planned sessions) are compared and the best fitting model is chosen provided it fits the data reasonably well. In the analysis of continuous outcomes the univariate general linear model is used. If the assumptions of a regression are not fulfilled, a non-parametric test is used (Mann-Whitney).

All outcomes are analyzed using regression analyses, including the binary intervention indicator. The primary results are those adjusted by the protocol-specified stratification variables and (where measured) the baseline value as covariates. In an exploratory analysis the analyses will be repeated with the categorical variable ID-group (identity code of the group) as an additional covariate, and it will be tested if the outcome depends on the treatment group. Then it will be tested if ID-group and the intervention indicator interact. If so, subgroup analyses of the various treatment groups will be conducted.

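### Patients are treated in arm-specific therapy groups, but the sample size and primary model assume independence; if attendance is correlated within groups, the test exceeds 5% and the stated power is too high

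*Protocol article*

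**What the plan says.** **Sample size.** The section on sample size estimation opens with "We are planning a trial of independent experimental participants and control participants randomized at a 1:1 ratio". It expects that "participants in the experimental group attend at least three more sessions than the participants in the control group", takes an SD of six sessions, and arrives at 64 per arm (128 in total) for 80% power and 85 per arm (170 in total) for 90%. It mentions no ICC, cluster size or design effect.

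**Delivery.** Under Structure: "There are seven patients and two therapists in each group". These groups are slow-open, so a new patient enters when another finishes. Under Therapists, each of the fifteen therapists is placed in a control group and in an experimental group. The Discussion likewise speaks of control groups and experimental groups in the plural. Patients are thus randomised one by one, but each therapy group sits in a single arm.

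**Expected dependence.** The Background section on dropout says that in group therapy dropout can harm the remaining members, sometimes as a wave "with dropouts begetting other dropouts".

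**Analysis.** Under Statistical analysis plan, Outcomes, the primary attendance result comes from a Poisson or negative binomial regression. It contains the arm indicator, the stratification variables and, where measured, the baseline value. Therapy group enters only later: "In an exploratory analysis the analyses will be repeated with the categorical variable ID-group". That step is followed by a test of whether outcome depends on the group and by a test of the interaction between group and arm.

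**The concern.** When groups are nested in arm, any variation between groups adds to the variance of the arm contrast. A model without a group term leaves that variance out of the standard error. A negative binomial model does not help here: it allows for extra variation between patients, not for correlation between members of the same group.

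The exploratory step does not close the gap. Since every group belongs to one arm, the group indicators for the experimental groups add up to the arm indicator, so the arm effect cannot be separated from a fixed group factor. The interaction of group and arm cannot be estimated at all, because no group is observed under both arms.

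If the ICC is positive, the error runs towards false positives in the confirmatory test. Under Multiplicity, a significant attendance result opens the test of the secondary outcome (EDE). That test has the same weakness if EDE scores are also correlated within groups.

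**Working it through.** **Inputs from the article.** Difference 3 sessions; SD 6; n = 64 or 85 per arm; two-sided 5%; seven patients per group; fifteen therapists, two per group.

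**Assumed, because the article gives no value.** ICC of 0.01, 0.02, 0.05 and 0.10; cluster size m = 7, the only group size stated.

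**Step 1: reproduce the stated figures.** Under independence SE = 6 × √(2/n).
- n = 64: SE = 1.061 and 3/1.061 = 2.83. The noncentral t gives 80.1% power (normal approximation 80.7%).
- n = 85: SE = 0.920 and 3/0.920 = 3.26. The noncentral t gives 90.0% power (normal approximation 90.3%).

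The stated sizes are met exactly under independence, so they contain no allowance for clustering.

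**Step 2: add clustering.**
- Design effect: DE = 1 + (m − 1) × ICC.
- Type I error of the unadjusted test: 2 × [1 − Φ(1.96/√DE)].
- Power of a test that holds its level: normal approximation with SE = 6 × √(2 × DE/n).

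Example for m = 7, ICC 0.05: DE = 1 + 6 × 0.05 = 1.30. Type I error = 2 × [1 − Φ(1.96/1.140)] = 8.6%. At n = 64, SE = 6 × √(2.60/64) = 1.209, 3/1.209 = 2.48, and power = Φ(2.48 − 1.96) = 70%.

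| ICC (m = 7) | DE | Type I error, unadjusted test | Power, N=128 | Power, N=170 |
|---|---|---|---|---|
| 0 | 1.00 | 5.0% | 81% | 90% |
| 0.01 | 1.06 | 5.7% | 78% | 89% |
| 0.02 | 1.12 | 6.4% | 76% | 87% |
| 0.05 | 1.30 | 8.6% | 70% | 82% |
| 0.10 | 1.60 | 12.1% | 61% | 73% |

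A simulation with nine groups of seven per arm (20,000 runs per setting, unadjusted t-test) gave type I errors of 5.5%, 6.3%, 8.7% and 12.1% for ICC 0.01 to 0.10, in line with the formula.

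**Step 3: sensitivity to the number of groups.** If each therapist has exactly one group per arm, there are 15/2 = 7.5 groups per arm, or about 15 in all. Then m = 64/7.5 = 8.5 at N=128 and 85/7.5 = 11.3 at N=170. For ICC 0.02, 0.05 and 0.10 the normal-approximation power is 75%, 67% and 57% at N=128, and 84%, 75% and 63% at N=170. With a t reference on 15 − 2 = 13 degrees of freedom it is 68%, 61% and 51%, and 78%, 69% and 56%. Part of that last drop comes from the few degrees of freedom alone: with 13 df and an ICC of zero, power is already 74% and 85%.

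**The case against.** The strongest reply is that the harm is conditional. A reader might infer that the primary test is known to be anti-conservative. The article does not show that: it gives no ICC, and at an ICC of 0.01 the effect is small (5.7%; power 78% and 89%). A reader might also take the Background to say that dropout does spread within groups. It says that this can happen and sometimes does, in general literature on dropout, and it says nothing about EDE scores. Both limits stand. What remains is that the authors' own rationale makes a positive ICC for attendance plausible, while the plan allows for none.

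Shared therapists are a weaker source of inflation than they look. Therapists work in both arms (each of them according to the Therapists section, most of them according to the Discussion), so a therapist effect common to both arms partly cancels in the contrast. Slow-open turnover also means that members overlap only partly in time. Both lower the effective correlation; neither removes the part specific to a group.

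The count of about 15 groups is inferred from the therapist numbers, and the article does not exclude more. With m = 7, power at N=170 stays at or above 80% up to an ICC of about 0.06, though 170 is to be reached only if possible. The calculations also use an unadjusted comparison of means, whereas the planned model is a rate regression adjusted for diagnosis and treatment type, which would absorb between-group variance due to those factors. The figures are illustrations, not this trial's operating characteristics.

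Finally, it would be wrong to say that the plan ignores groups. The test of whether outcome depends on group has some diagnostic value, but it does not correct the primary standard error.

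**Conclusion.** The point holds in conditional form. The sample size assumes independence, the primary model has no group term, and the exploratory group factor cannot supply a valid arm comparison; all three follow from the article. If the ICC is above zero, the planned attendance test exceeds 5%, and so does the EDE test if EDE scores are correlated within groups. At m = 7 and an assumed ICC of 0.01 to 0.10, the type I error is about 5.7% to 12.1%. Power of a level-holding test is 78% to 61% at N=128 and 89% to 73% at N=170. With only about 15 groups the figures are worse.

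The two harms are alternatives and should not be added together: inflated type I error belongs to the unadjusted test, and reduced power to a test that accounts for groups. Direction is well supported given a positive ICC; size is not known from the article.

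**What to change.** **Analysis (Statistical analysis plan, Outcomes).** Make the primary attendance and EDE analyses account for therapy group. Either use a random intercept for group within arm, or use cluster-robust standard errors at group level with a small-sample correction, with degrees of freedom based on the number of groups in either case. Let this replace the fixed group covariate and its interaction with arm.

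**Power (Sample size estimation and Table 3).** Restate power at N=128 and N=170 over an assumed ICC range of 0.01 to 0.10 with a stated cluster size, in place of the 80% and 90% claims. State the actual number of groups per arm, since the degrees of freedom depend on it.

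**Cost.** Slightly wider confidence intervals and a less favourable stated power. The group identifier is already recorded, so no new data and no change to treatment are needed.
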